**Figure 1 F1:**
[figure not shown]
Flow of subjects randomized to receive repetitive magnetic stimulation (rMS) at HT7 or repetitive transcranial magnetic stimulation (rTMS) at right dorsolateral prefrontal cortex (r-DLPFC) or waiting treatment.

The clinical trial results will be reported according to the Standards for Reporting Interventions in Clinical Trials of Acupuncture statement.^[19]^

### Ethics

2.2

This study has been approved by the ethics committee of Shaanxi Province Hospital of traditional Chinese Medicine ([2019] ethical review No. 08), and registered on http://www.chictr.org.cn/index.aspx with the ID ChiCTR1900026844. Informed consents will be obtained from all the subjects involved. Any modification of the study protocol or informed consent that may affect the rights and interests of the participants or the implementation of the study shall be reported to the Ethics Committee for approval. In case of any serious adverse event in the trial, the ethics committee shall promptly review it and recommend written modifications, including sufficient authority to suspend the trial.

### Study population

2.3

#### Inclusion criteria

2.3.1

1.Subjects, diagnosed with primary insomnia, insomnia severity index (ISI) scores >7 points,^[20]^ according to the Diagnostic and Statistical Manual of Mental Disorders-Fifth Edition (DSM-V), F51.01^[21]^;2.Subjects, diagnosed with initial CI (course of the disease ≥3 months and frequency ≥3 times/week)^[8]^;3.Subjects, aged between 18 and 65 years old, right-handed, male or female;4.Cooperation during examination, without aphasia and severe cognitive disorders;5.Sign the informed consent.

#### Exclusion criteria

2.3.2

1.Subjects, diagnosed with secondary insomnia, such as mental disorders (depression, anxiety, schizophrenia, diphasic, etc) or physical diseases (pain, stroke, coronary heart disease, tumor, etc) or other nonpathologic factors (poor sleep hygiene, jet lag, shift work, etc);2.With severe depression and anxiety (PHQ-9 scores ≥20 points; GAD-7 scores ≥19 points),^[22]^ high risk of sleep apnea (>3 items in the Stop Bang questionnaire), aphasia and severe cognitive dysfunction (MMSE scores <17 points)^[23]^;3.With severe heart disease, malignancy, kidney, and liver function insufficiency;4.Dependence or abuse of alcohol or drugs;5.With metal foreign bodies (cochlear implant, built-in pulse generator, aneurysm clip, stent, etc) at the treatment sites within 30 cm depth under the skin;6.Participation in any other clinical trial or taking benzodiazepines in recent 2 weeks or receiving TMS, transcranial direct current stimulation, electroconvulsivetherapy, acupuncture and other treatments regularly over the last 1 month;7.Pregnant or lactating women.

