##### rMS at HT7 acupoint

2.7.1.1

The rTMS therapeutic apparatus (CCY-II model; Wuhan YiRuiDe Medical Supplies New Technology Co Ltd, Wuhan, China) were used. rTMS is applied to treat CI according to the modern neuro-rehabilitation theory. Acupoint is only left HT7 (*shenmen*) acupoint according to the TCM theory. After preparation, test the resting motor threshold (RMT): the participants will take the sitting position, keep the mood stable and the muscles relaxed. During stimulating M1 region, the coil will be tangent to the scalp, and it will be advisable to adjust the coil to get the maximum amplitude and the best repeatability of motor evoked potential. The stimulus intensity will begin from 30% and gradually increase at a rate of 2.5%. The minimum stimulus intensity (RMT) will be the abdominal contraction in the abductor pollicis brevis muscles of contralateral thumb in 5 out of 10-times consecutive stimuli; locate the stimulus area: the stimulation coil will be placed at the left HT7 acupoint (on the anteromedical aspect of the wrist, radial to the flexor carpi ulnaris tendon, on the palmar wrist crease) (Fig. 2); set the stimulus parameters: the standard mode is selected as the stimulus mode, for instance the frequency as 1 Hz, the total pulses number as 1800, and the intensity as 25% RMT.^[24]^ Start the stimulation after checking the above parameters, and then remove the coil flap after the stimulation. Participants will be treated 2 sessions per day for 10 consecutive days.

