##### rTMS at r-DLPFC

2.7.2.1

Low-frequency (1 Hz) rTMS at r-DLPFC is recommended for sleep disorders in the *Chinese experts consensus on rTMS* (level of evidence: level II/III)^[12]^ and *Guidelines for The Diagnosis and Treatment of Insomnia in China*.^[25]^ After preparation, test RMT: the measurement is same as the experimental group; locate the stimulus area: the stimulation coil will be placed tangent to the scalp on the r-DLPFC (8 cm in front of the midpoint of the connection between 2 ear tips, and then 6 cm toward the right side); set the stimulus parameters: the intensity is selected 100% RMT. Other parameters are same as the experimental group. Participants will be treated 2 sessions per day for 10 consecutive days.

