#### Waiting-list control group

2.7.3

The participants in the waiting group will not be treated within 10 days during the study period, and then treated same as the positive control group from the 11th day.

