### Randomization

2.12

After recruitment, the patients who meet the eligibility criteria would be randomly and equally divided into 3 groups at a ratio of 1:1:1 with random number table method. Each subject will be registered with a unique ID. After the clinical screening and getting the informed consent forms, subjects will be assigned to experimental group (rTMS at HT7), positive-control group (rTMS at r-DLPFC), and waiting-list control group (no treatment) randomly. Each subject will receive the different stimulation forms, even no stimulating, whereas all subjects will be aware of the grouping.

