#### Primary outcomes

2.13.1

We will use univariate repetitive measurement deviation analysis with ISI scores and RMT before and the 10th day of treatment, 30th day of follow-up as the outcomes. A significant effect of group indicates that the ISI scores and RMT are different between groups after intervention.

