## Discussion

3

The CI is a persistent insomnia disease, which the course of the disease is >3 months and frequency more than 3 times/wk.^[8]^ The onset of CI is affected by many factors involving age, gender, medical history, stress events, personality traits, inheritance, mental disorders, physical diseases, and so on.^[25]^ Refer to the diagnostic criteria of CI, CI patients who are long-term subjected to insomnia problem, will bring direct or indirect harm to the society. Therefore, according to patients symptoms combined with rating scale, we hope to obtain high quality study data from this preliminary clinical trial that could provide reliable basis to future multicenter research.

The rTMS at r-DLPFC which is chosen as a positive controlled therapy for CI in this study has been recommend by experts consensus.^[12]^ As a noninvasive stimulation technique, rTMS can test changes in motor evoked potential, brain electrical activity, cerebral blood flow, metabolism, and brain functional status from the changes in neural activity.^[27]^ Besides, DLPFC plays an important role in our cognition, decision, and memorization, which is always as an effective stimulating target for the treatment of insomnia and depression, especially low-frequency (1 Hz) rTMS at DLPFC.^[12]^ However, rTMS on the static head directly might be limited with some potential risks like scalp tingling and burning, hearing impairment, even seizure, especially for the ones with metal implants in skull or body.^[28]^ Moreover, it is inconvenient for insomnia patients to receive continuing care in daily life with rTMS at DLPFC. For this, rMS at acupoint on CI may be a promising alternative therapy. Acupoints have been widely used and received in clinical practice in China.^[29]^ Patients in China are usually familiar with acupuncture, and expect to receive acupuncture treatments. Thus, since acupuncture is often regarded as an invasive operation,^[30]^ it is difficult to replicate its manipulations in clinic and design a nonpenetrating sham acupuncture in trial.^[31]^ Hence, aim to improve subjects compliance and achieve acupoint effect, we choose rMS at HT7 acupoint in the experimental group in a high-quality randomized controlled trial. Although studies have showed the efficacy of rTMS for CI,^[32,33]^ it is still lack rMS at acupoint randomized controlled trial, as well as the relevant mechanism research.

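### Exclusion 5 states its 30 cm metal limit as a depth at the treatment sites, so it does not reliably exclude a trunk-sited pulse generator, a device it lists

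*Protocol article*

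**What the plan says.** The only implant criterion in the Protocol article is exclusion 5 in section 2.3.2: "With metal foreign bodies (cochlear implant, built-in pulse generator, aneurysm clip, stent, etc) at the treatment sites within 30 cm depth under the skin".

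The coil positions are set out elsewhere:

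- **Left HT7**, at the wrist, is the treatment site of the experimental arm (section 2.7.1.1).
- **r-DLPFC** is the treatment site of the positive-control arm, located "8 cm in front of the midpoint of the connection between 2 ear tips, and then 6 cm toward the right side" (section 2.7.2.1). The waiting-list arm is "treated same as the positive control group from the 11th day" (section 2.7.3).
- **M1** is pulsed to find the RMT: "During stimulating M1 region, the coil will be tangent to the scalp" (section 2.7.1.1). For the positive control: "After preparation, test RMT: the measurement is same as the experimental group" (section 2.7.2.1). RMT is a primary outcome at three visits (section 2.9) and is compared across groups: "A significant effect of group indicates that the ISI scores and RMT are different between groups after intervention" (section 2.13.1).

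Eligibility is settled before allocation: "After the clinical screening and getting the informed consent forms, subjects will be assigned to experimental group" (section 2.12). On risk, the Discussion says that rTMS on the head carries "some potential risks like scalp tingling and burning, hearing impairment, even seizure, especially for the ones with metal implants in skull or body".

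**The concern.** The rule names devices that matter for magnetic stimulation, then ties them to a place and a depth that do not fit them. A built-in pulse generator may sit in the chest or abdomen, which is neither the left wrist nor the right frontal scalp. A screener who follows the sentence word for word could admit such a candidate, who would then receive scalp pulses for RMT and, in two of the three arms, r-DLPFC treatment. The Discussion places no such limit on where in the body the implant sits. At stake is participant safety at screening; sample size, power and the analysis are untouched.

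**Working it through.** The plan gives no figure to reproduce here. The check reads the rule in its two possible senses against each coil position. All body dimensions below are assumptions, because the article gives none.

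**1. The figure as a depth.** Assume a wrist 3 to 7 cm thick and a head 14 to 22 cm across. Both are below 30 cm, so a 30 cm depth excludes nothing from consideration at either place. The working limit becomes location at a treatment site: left HT7 or r-DLPFC. A trunk generator is at neither, so its carrier passes.

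**2. The figure as a distance from the coil.** The listed devices, the plural for sites and screening before allocation all point to this sense, applied to every candidate.

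*M1.* With r-DLPFC 8 cm forward and 6 cm right of the ear-tip midpoint (section 2.7.2.1), assume hand M1 lies 4 to 6 cm lateral to that midpoint on either side, on a flat-scalp approximation.

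- Nearest (right side, 6 cm lateral): √(8² + (6 − 6)²) = 8.0 cm.
- Farthest (left side, 6 cm lateral): √(8² + (6 + 6)²) = √208 = 14.4 cm.
- Margin inside 30 cm: 30 − 14.4 = 15.6 cm to 30 − 8.0 = 22.0 cm.

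So M1 is well covered. With a head at most 22 cm across, so is the rest of the head.

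*Trunk generator, from r-DLPFC.* Assume a chest unit with a vertical drop of 25 to 45 cm and a horizontal offset of 5 to 15 cm.

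- Shortest: √(25² + 5²) = 25.5 cm, inside.
- Drop 25, offset 15: √(25² + 15²) = 29.2 cm, inside.
- Drop 30, offset 5: √(30² + 5²) = 30.4 cm, outside.
- Longest: √(45² + 15²) = 47.4 cm, outside.

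The range straddles the limit, and any drop of 30 cm or more is outside whatever the offset.

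*Trunk generator, from left HT7.* The article fixes no arm position during treatment. With the wrist on the lap, an abdominal unit might be 10 to 25 cm away (assumption), hence inside; a chest unit could be inside or outside.

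On the distance reading, then, the rule may or may not catch the device, and the article does not supply what would decide it.

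**3. Other criteria.** Exclusion 1 covers insomnia secondary to conditions such as stroke or coronary heart disease, and exclusion 3 covers severe heart disease. They remove some device carriers. They do not remove someone with a pacemaker but no severe heart disease, or with a non-cardiac stimulator.

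**The case against.** The best defence is that the literal reading is improbable. It would leave the listed cochlear implant and pulse generator almost without application, and the physicians are trained in rTMS (sections 2.7 and 2.14). If 30 cm is a safety distance, letting through metal beyond it is what the rule is for; the Discussion sentence is general and gives no distance. The article is also condensed, and a device checklist may exist in a document that is not shown.

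Much of this stands. It rules out three stronger readings that a reader might infer:

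- *That M1 is left unscreened, or that HT7 candidates are checked only at the wrist.* Screening precedes assignment, so on the distance reading every candidate is checked against r-DLPFC, which covers M1. Leaving M1 unnamed is a wording point.
- *That most chest generators fall outside 30 cm.* How many do depends on which dimensions are assumed, and measuring from r-DLPFC alone ignores the HT7 coil.
- *That a generator beyond 30 cm is shown to be unsafe.* The documents contain no evidence on this at any distance.

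The defence does not remove the defect in the sentence. Eligibility is stated here, and a criterion that lists a device without reliably excluding it is badly fixed, which is different from detail left to another document.

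**Conclusion.** The point holds as a minor safety correction to wording, with medium confidence. On the literal reading a trunk-sited pulse generator is admissible; on the probable distance reading the outcome is indeterminate. That conclusion needs only that such a generator is at neither treatment site and that its distance from the coils varies with build and posture; the centimetre ranges illustrate this and are not estimates.

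The documents give no implant frequency, so the number affected is unknown and probably small. For the HT7 arm (15 participants, or 54 / 3 = 18 on the total in section 2.1), RMT testing is the only scalp stimulation.

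**What to change.** Replace exclusion 5 with a rule applied to every candidate before baseline RMT and randomisation. Exclude anyone with:

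- (a) an implanted electronic device, such as a pulse generator or cochlear implant, wherever it is sited;
- (b) intracranial metal, such as an aneurysm clip or stent; or
- (c) other implanted metal within 30 cm of any coil position, naming M1, r-DLPFC and left HT7.

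Delete the reference to depth beneath the skin. The sponsor may also wish to say whether dental metalwork is exempt, since (c) would otherwise catch it.

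The cost is a one-sentence amendment, one change to the screening checklist, and the loss of a few candidates with remote devices.

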#### Withdrawal criteria

2.3.3

1.Violation of the inclusion criteria and clinical trial protocol or fulfillment of the exclusion criteria;2.Do not receive 10 consecutive treatment days or receipt of <20 rMS sessions;3.Serious adverse events;4.Loss to follow-up;5.Withdrawal of consent by the subject or a legal representative;6.Self-replacement of the treatment package that could affect the study results without permission from the investigator.

### Study settings and recruitments

2.4

The present study will be conducted in the Shaanxi Province Hospital of Traditional Chinese Medicine.

Participants with the diagnosis of CI will be recruited at above-mentioned hospital, who mainly come from hospital wards and clinics. Besides, posters, leaflets, and the routine free clinics will be also helpful. Sure, except these, the hospital websites, WeChat, and Microblogging are powerful advocacy media.

### Study group

2.5

Forty-five participants who meet the criteria with informed consents will be selected. The subjects will be randomly divided into 3 groups in a 1:1:1 ratio, namely the experimental group, positive-control group and waiting list control group, 15 cases in each group.

### Study time

2.6

This clinical study will be conducted from August 1, 2019 to August 1, 2021.

### Interventions

2.7

Interventions are selected base on the theory of TCM and expertise. The physicians involved have received their practitioners’ license from China's National Health and Family Planning Commission as well as acupuncture and rTMS clinical skill training, who have worked for more than 3 years. Subjects in experimental group will receive rMS at HT7, and others in control group will receive rTMS at r-DLPFC or waiting treatment. Besides, if the symptoms were severe or do not improve during the treatment or the waiting period, Eszopiclone tablets (3 mg Qn) would be allowed.

#### Experimental group

2.7.1

##### rMS at HT7 acupoint

2.7.1.1

The rTMS therapeutic apparatus (CCY-II model; Wuhan YiRuiDe Medical Supplies New Technology Co Ltd, Wuhan, China) were used. rTMS is applied to treat CI according to the modern neuro-rehabilitation theory. Acupoint is only left HT7 (*shenmen*) acupoint according to the TCM theory. After preparation, test the resting motor threshold (RMT): the participants will take the sitting position, keep the mood stable and the muscles relaxed. During stimulating M1 region, the coil will be tangent to the scalp, and it will be advisable to adjust the coil to get the maximum amplitude and the best repeatability of motor evoked potential. The stimulus intensity will begin from 30% and gradually increase at a rate of 2.5%. The minimum stimulus intensity (RMT) will be the abdominal contraction in the abductor pollicis brevis muscles of contralateral thumb in 5 out of 10-times consecutive stimuli; locate the stimulus area: the stimulation coil will be placed at the left HT7 acupoint (on the anteromedical aspect of the wrist, radial to the flexor carpi ulnaris tendon, on the palmar wrist crease) (Fig. 2); set the stimulus parameters: the standard mode is selected as the stimulus mode, for instance the frequency as 1 Hz, the total pulses number as 1800, and the intensity as 25% RMT.^[24]^ Start the stimulation after checking the above parameters, and then remove the coil flap after the stimulation. Participants will be treated 2 sessions per day for 10 consecutive days.

**Figure 2 F2:**
[figure not shown]
Location of Shenmen (HT7) Acupoint. Longxiang H. WHO Standard Acupuncture Point Locations in the Western Pacific Region (Chinese-English bilingual edition). Beijing: People's Medical Publishing House, 2010.

#### Positive-control group

2.7.2

##### rTMS at r-DLPFC

2.7.2.1

Low-frequency (1 Hz) rTMS at r-DLPFC is recommended for sleep disorders in the *Chinese experts consensus on rTMS* (level of evidence: level II/III)^[12]^ and *Guidelines for The Diagnosis and Treatment of Insomnia in China*.^[25]^ After preparation, test RMT: the measurement is same as the experimental group; locate the stimulus area: the stimulation coil will be placed tangent to the scalp on the r-DLPFC (8 cm in front of the midpoint of the connection between 2 ear tips, and then 6 cm toward the right side); set the stimulus parameters: the intensity is selected 100% RMT. Other parameters are same as the experimental group. Participants will be treated 2 sessions per day for 10 consecutive days.

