The short-term efficacy of sleep agents has been proved, but they often lead to a series of side effects, like daytime dysfunction, sleep driving, abnormal behavior, and depression deterioration. Moreover, it does exist addiction, which might make patients resistance and low compliance for long-term users.^[9,10]^ Due to the lack of cultural background and diplomats in China, the implementation of cognitive behavioral therapy in basic hospitals and general hospitals is rarely used at present. Thus, it is essential to select an effective, safe, no side effects, and no addiction sleep method. Repetitive transcranial magnetic stimulation (rTMS) is a noninvasive neuroregulatory technique in line with the above characteristics, which has been widely used in clinic by reducing cortical excitability in CI patients.^[11]^ Low-frequency (1 Hz) rTMS at bilateral frontal or parieooccipital regions is recommended for sleep disorders in the *Chinese experts consensus on rTMS* (level of evidence: level II/III).^[12]^ However, the rTMS for patients with intracranial metal implants, stents, glaucoma, and hypertension is limited. In traditional Chinese medicine (TCM), insomnia is an appropriate disease in the acupuncture spectrum of diseases. *Shenmen* acupoint (HT7) is the *yuan* acupoint of Heart-Channel, the most frequently selected for insomnia.^[13]^ Acupuncture at HT7 acupoint can activate related brain regions highly associated with improving sleep, emotional, and cognition.^[14,15]^ Thus, the problem of acupuncture therapy is that its manipulations are difficult to replicate, and some patients cannot tolerate repeated pain stimulation. Studies have shown that the effects of repetitive magnetic stimulation (rMS) at acupoints can be quantified, similar to acupuncture effect,^[16]^ noninvasive and painless. In particular, low frequency (1 Hz) rMS at HT7 acupoint can make brain activity in good order and reduce brain excitability for the healthy.^[17]^ Furthermore, low frequency (1 Hz) rMS at HT7, PC6 and SP6 can be also good for the subhealth insomnia ones in enhancing interaction between brain regions, increasing transmission speed and efficiency between brain networks, and improving brain cognitive function.^[18]^ However, there are few clinical studies on low frequency (1 Hz) rMS at HT7 acupoint for CI.

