### Study design

2.1

This is a single-center, randomized, positive-controlled, noninferiority clinical pilot trial. A total of 54 participants will be randomized into 3 groups at a ratio of 1:1:1. Participants in the treatment group will be treated with rMS at HT7 acupoint. Participants in the control group will be treated with rTMS at r-DLPFC or waiting treatment.

The whole study period is 35 days, including 5-day baseline observation, 10-day treatment, and 20-days follow-up. Subjects will be evaluated with scales for clinical efficacy before and the 10th day of treatment, 30th day of follow-up, and monitored by rMS/rTMS for therapeutic mechanism before and the 10th day of treatment, 30th day of follow-up (Fig. 1).

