### Statistical analysis

2.13

Data analysis will be based on intention-to-treat analysis and/or per-protocol analysis principle in the light of data missingness. We will also evaluate the group effect by comparing the analysis results between the above 2 data sets to evaluate robustness of our analytical results.

All data will be analyzed using SPSS23.0 (v23.0; SPSS Inc, Chicago, IL) by 3rd-party statistician. A *P* value <.05 will be considered as significant. Descriptive statistics will be performed with mean, standard deviation, maximum, minimum, and so on by groups and time.

Baseline characteristics of patients will be summarized by groups and compared with Chi-squared for categorical variables, and analysis of variance (ANOVA) (normal distributions) or Kruskal–Wallis test (non-normal distributions) for the continuous variables. Primary and secondary outcomes according to the measurement times are applicable to univariate repetitive measurement deviation analysis or ANOVA or Kruskal–Wallis test. If there is a violation of distribution assumption, appropriate transformation will be used.

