Our protocol is just a pilot study with several limits including the small sample size, open-blinding, and short period of observation time. However, we try our best to attempt to minimize the biases that may influence study results. Finally we intend to demonstrate the hypothesis that rMS at HT7 acupoint as an alternative may be validated for CI.

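### The primary rule, a group effect across baseline, day 10 and day 30, does not isolate the day-10 waiting-list contrast needed to show that r-DLPFC worked before HT7 is called an alternative to it

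*Protocol article*

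**What the plan says.** Section 2.1 of the protocol article sets the aim: "This is a single-center, randomized, positive-controlled, noninferiority clinical pilot trial". The Discussion closes with the intended conclusion: "we intend to demonstrate the hypothesis that rMS at HT7 acupoint as an alternative may be validated for CI".

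Section 2.13.1 gives the primary analysis: a univariate repeated-measures analysis of ISI and RMT at baseline, day 10 and day 30. It also says how the result will be read: "A significant effect of group indicates that the ISI scores and RMT are different between groups after intervention". Section 2.13 sets the threshold, a P "value <.05 will be considered as significant". The article names no pairwise comparison and no condition on the control's performance.

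Section 2.7.3 describes the third arm: "The participants in the waiting group will not be treated within 10 days during the study period". From day 11 these participants receive the same treatment as the positive control.

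The basis for the control is worded in two ways under one citation and one evidence level (II/III). In the Introduction, low-frequency "rTMS at bilateral frontal or parieooccipital regions is recommended for sleep disorders in the" expert consensus. In section 2.7.2.1, low-frequency "rTMS at r-DLPFC is recommended for sleep disorders in the" same consensus, with a national insomnia guideline as a second source. The Discussion repeats the second version: "The rTMS at r-DLPFC which is chosen as a positive controlled therapy for CI in this study has been recommend by experts consensus".

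**The concern.** Calling a new treatment an alternative to an active control makes sense only if the control had an effect in the trial at hand. If r-DLPFC did nothing here, similarity to it says nothing about whether HT7 improves sleep. A properly specified noninferiority test does not remove this problem, because it compares the two stimulations only with each other.

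The trial includes an arm that could settle the matter, the waiting list, but that arm is informative as an untreated comparator only at day 10. The stated rule spreads the comparison over three occasions and three groups and reads the result only as a difference between groups. It does not show whether r-DLPFC beat no treatment. At stake is a claim that HT7 is a valid alternative when neither stimulation lowers ISI.

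**Working it through.** **Inputs from the article.** There are three arms at 1:1:1. The abstract and sections 2.5 and 2.11 give 45 participants, so 45/3 = 15 per arm. Section 2.1 gives 54, so 54/3 = 18 per arm. That discrepancy is a separate matter, and both sizes are used here. The significance level is 0.05, taken as two-sided because the article does not say.

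**Assumptions.** The article gives no margin, SD, effect size or power, so there is no sample-size calculation to reproduce. I take a normal outcome at a single time point, SD = 1, margins of 0.5, 0.8 and 1.0 SD, and no dropout.

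**Step 1: what the stated rule sees.** A group main effect averages the occasions. Randomisation makes the expected baseline difference zero. Suppose r-DLPFC beats the waiting list by δ at day 10, and the gap has closed by day 30 because the waiting list was treated from day 11. The averaged difference is then (0 + δ + 0)/3 = δ/3. A closed gap at day 30 is an assumption, but some dilution follows from section 2.7.3.

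Even an omnibus test at one time point with 15 per arm leaves the question open (100,000 simulated trials per scenario):

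| Truth | Omnibus test not significant |
|---|---|
| Neither stimulation works | 95% |
| Both better than waiting list by 0.8 SD | 42% |
| Both better by 1.2 SD | 8% |

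A non-significant result fits either truth. A significant one does not say which groups differ or in which direction.

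**Step 2: a noninferiority test when neither works.** The test passes if (HT7 mean − r-DLPFC mean) + t(0.975, 28) × s × √(2/15) is below the margin, where lower ISI is better. With s = 1 the added term is 2.048 × 0.365 = 0.748 SD. At a margin of 0.5 SD the observed difference must therefore be below 0.5 − 0.748 = −0.248 SD. At 1.0 SD it must be below +0.252 SD.

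**Step 3: add the condition.** Require also that r-DLPFC beat the waiting list (two-sided P < .05, in the right direction). With no true effect this alone happens in about 2.5% of trials.

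| Per arm | Margin (SD) | Passes without condition | Passes with condition |
|---|---|---|---|
| 15 | 0.5 | 26% | 0.1% |
| 15 | 0.8 | 56% | 0.5% |
| 15 | 1.0 | 75% | 0.9% |
| 18 | 0.5 | 31% | 0.1% |
| 18 | 0.8 | 65% | 0.6% |
| 18 | 1.0 | 83% | 1.1% |

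The joint rates are below the simple product (at 15 per arm and 0.5 SD, 0.264 × 0.0248 = 0.65% against 0.09%). The reason is that both comparisons share the r-DLPFC arm: a chance low mean there helps the condition and hurts HT7.

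**Step 4: power of the condition.** From the noncentral t with 28 df and noncentrality d × √(15/2), power at 15 per arm is 26%, 56%, 75% and 89% for true effects of 0.5, 0.8, 1.0 and 1.2 SD. At 18 per arm it is about 31%, 65%, 83% and 94%. These repeat the unconditioned pass rates above because the formula is the same, with the true effect in place of the margin.

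**The case against.** The strongest reply is that this is a condensed article on a pilot. Ordered comparisons and conditions on claims are often left to a fuller document, and the waiting list is already one of the groups in the primary analysis. The conclusions are also hedged as preliminary. This stands in part: silence on pairwise contrasts does not show that none is planned. But section 2.13.1 is not silent. It fixes the analysis and its interpretation, and neither answers the aim stated in section 2.1 and the Discussion.

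A reader might infer that the plan would declare the two stimulations equivalent, or would take a non-significant group effect as proof that HT7 works. The documents do not support that. They speak of noninferiority and of an alternative, never of equivalence, and attach no positive claim to a non-significant result.

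A reader might also infer that the consensus does not support the control. That too goes beyond the text. The r-DLPFC is a frontal site, so section 2.7.2.1 may be a narrower paraphrase of the Introduction, and it cites a second source. What the consensus says cannot be settled from the article.

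Two further objections stand in full. The pass rates describe a noninferiority test at assumed margins, not an error rate of the plan as written. And the condition is weak at this sample size.

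**Conclusion.** The concern holds in a limited form. The stated primary rule neither isolates the day-10 untreated contrast nor separates two working treatments from two that do not work, so it cannot carry the intended conclusion about HT7.

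The size is conditional. With normal outcomes, no true effects and assumed margins of 0.5 to 1.0 SD, false support for HT7 would arise in about 26% to 75% of trials at 15 per arm without the condition. With it, the figure is at most about 1%, including at 18 per arm.

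The condition is necessary but not sufficient. Section 2.12 says that all subjects know their group, so a gain over an untreated list on ISI may partly reflect expectation. Eszopiclone, permitted during treatment and waiting (section 2.7), may also blur the contrast.

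The differing accounts of the consensus are a minor, separate inconsistency. Resolving them would not change the need for the internal comparison.

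**What to change.** Add to section 2.13.1 two prespecified comparisons on ISI at day 10, each with an estimate and 95% CI adjusted for baseline ISI: r-DLPFC against the waiting list, and HT7 against the waiting list. State that HT7 will be called an alternative only if the first interval excludes zero in favour of r-DLPFC. This comes in addition to the HT7 versus r-DLPFC comparison and does not replace it. Otherwise, report HT7 versus r-DLPFC as inconclusive about efficacy and interpret only HT7 versus the waiting list.

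This needs wording and two contrasts, with no new visits: ISI is already scheduled at day 10, before the waiting list starts treatment.

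The price is a claim that will often not be reached. If both stimulations truly beat the waiting list by 0.8 SD and are equal to each other, then at 15 per arm and an assumed margin of 0.8 SD the chance of the claim falls from 56% to 25%. With true effects of 1.2 SD it falls from 56% to 47%. The protocol should say so, as a limit of a pilot this small.

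Separately, reconcile the Introduction, section 2.7.2.1 and the Discussion on which stimulation site the cited consensus recommends.
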